#### Heart rate variability

Heart Rate Variability (HRV) will be measured using photoplethysmography (PPG) sampled at 135 Hz using Polar Verity Sense heart rate sensors. Each participant in the session will receive their own sensor and all sensors will be time synchronized. The measurement period will include the entire group-singing or audiobook club session. Additionally, we will measure pre- and post-singing/audiobook rest periods, each lasting 60 seconds as a baseline measure. PPG data will be imported to Kubios HRV Scientific software (version 4.1.1) which will allow for computation of Root Mean Square of Successive Differences (RMSSD) between adjacent peaks, a time-domain measurement of HRV. Synchrony of HRV between participants over the course of a session (i.e., between the two rest periods) will be assessed using time-frequency coherence analysis [117]. A pre-post comparison of HRV during rest periods will also be conducted for each participant to assess global changes in ANS activity over the course of a single session.

### Test procedure

Below, we list the three facets to the test procedure, noting that some occur over several sessions. For consistency and logistical pragmatics, we will aim to test all participants within two-week windows, relative to key training timepoints.

Consent and Screening—initial session.Macro Timepoint Testing—two sessions in a test booth:
Baseline (up to 2-weeks before training begins).Completion (up to 2-weeks after training ends).Micro Timepoint Testing—six sessions at the site of training:
Pre- and Post-session testing at Week 2.Pre- and Post-session testing at Week 7.Pre- and Post-session testing at Week 11.

#### Consent, screening, and demographic information

Data collectors will assess participant’s eligibility. This will consist of understanding and signing a participant information and consent form; completion of an audiological assessment to establish their level of unaided hearing loss (pure tone average testing at 500 Hz, 1000 Hz, 2000 Hz, and 4000 Hz); and passing the MoCA-H screener with a criterion score ≥ 24. If these inclusion criteria are met, participants will complete their demographic information in a questionnaire.

#### Macro timepoint testing

The purpose of the testing from *baseline* to *completion* is to examine any benefit from the training. Macro timepoint testing consists of the following behavioural measures presented in fixed order: CRM, EmoHI, FDL, BAT, SMRT, and MINT; and the following questionnaires: SF-12v2, HADS, CSES, SCS-R, EMO-CheQ.

The macro timepoint testing will occur on-site in an acoustically-treated test booth. The presentation level of behavioural measures will be calibrated to 65 dB with a sound-level meter measured at the participants’ position, which will be located 0.5 m directly in front of the loudspeaker. Data collectors conducting the macro timepoint tests will be blinded to the participants’ intervention and participants will be asked not to talk about their intervention during testing. Any instances of unintentional blinding (i.e., a participant informing the data collector of their participation) will be recorded. The participants will receive $20 CAD (or equivalent currency) for the consent and screening, and each macro timepoint testing session.

#### Micro timepoint testing

The purpose of the micro timepoint testing is two-fold. Firstly, to examine the physiological and psychosocial changes that occur from *pre-* to *post-session*; and secondly, to examine the cumulative longitudinal impacts on physiological measures for each intervention. Micro timepoint testing consists of HRV and the following questionnaires presented in fixed order: PANAS, IOS, SUDS.

The micro timepoint testing will occur on-site where the training occurs at: 1) Pre-session (directly before the intervention begins); and 2) Post-session (directly after intervention ends). Testing will involve biophysical measures and questionnaires (described in detail under the Test Battery and Test Procedure sections). These micro measures will be taken at the training sessions in Week 2, 7, and 11 and designed to be indicative of pre- and post-session measures corresponding to the start, middle, and end of the training program.

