### Micro-level hypotheses

H1. Group singing may lead to increases in positive mood—more so than the participants in the control group.H2. Group singing may foster greater feelings of social closeness—more so than the participants in the control group.

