#### Difference score and outlier rejection

Outliers due to technical errors will be removed. Univariate outliers on continuous independent and dependent variables will be rejected based on a boxplot method, wherein a data point is an outlier if it falls 1.5 times outside of the interquartile range. Because each group may have unique distributions, we plan to reject outliers based for each group individually. For each of the micro-level dependent measures, a difference score will be computed (i.e., *pre-* to *post-session*).

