For each micro-level dependent variable, three separate MLMs will be defined: 1) an intercept-only model; 2) a main-effect only model (DV_change_ ~ *group + time*) and 3) an interaction (DV_change_ ~ *group * time*) model. For micro-level models, the time variable will reflect the time point of the micro-level observation and will allow us to model changes between the group across time. Similarly, three separate MLMs will be defined for macro-level dependent variables: 1) an intercept-only model; 2) a main-effect only model (DV ~ *group + session*) and 3) an interaction (DV ~ *group * session*) model. For both macro and micro-level models we will use a hierarchical modeling technique to determine which model is the best fit to the data. Model fit parameters will be compared between the three models and results of the model with the best fit will be reported on. Upon the discovery of a significant interaction, a follow-up simple slope analysis will be used to examine the differences in time (e.g., *baseline* vs. *completion*) across groups. For all hypothesis tests, alpha values will be set at 0.05.

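### The micro-level models use only within-session difference scores, so the stated cumulative aim is not answered for resting heart rate variability levels

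*Protocol article*

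**What the plan says.** The section Micro timepoint testing gives two purposes. The first is physiological and psychosocial change from before to after a session. The second is "to examine the cumulative longitudinal impacts on physiological measures for each intervention". Measurements are taken before and after the sessions in Weeks 2, 7 and 11.

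The analysis sections then fix the dependent variable. Difference score and outlier rejection states: "For each of the micro-level dependent measures, a difference score will be computed". Modelling and inferential statistics states: "For each micro-level dependent variable, three separate MLMs will be defined". These are an intercept-only model, `DV_change ~ group + time` and `DV_change ~ group * time`. It adds that "the time variable will reflect the time point of the micro-level observation and will allow us to model changes between the group across time".

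For HRV, the section Heart rate variability plans a pre-post comparison of the rest periods "to assess global changes in ANS activity over the course of a single session". Synchrony between participants "will be assessed using time-frequency coherence analysis" over the part of the session between the two rest periods.

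The second micro-level hypothesis (H2) reads "Group singing may foster greater feelings of social closeness", relative to control. HRV is listed under Exploratory analyses.

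**The concern.** A cumulative effect on a physiological measure would naturally show as a shift in its resting level over the weeks: participants arrive at Week 11 with a different resting RMSSD from the one they had at Week 2. A shift of that kind raises the pre-session and post-session values together, and a difference score removes it. No stated model looks at the pre-session or post-session value across weeks.

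The protocol therefore states a purpose and fixes an analysis that cannot serve it for resting HRV. A null group-by-time result could be read as evidence of no cumulative impact when the model was never able to see one. If the level were examined later, that analysis would be post hoc.

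**Working it through.** **The plan's own figure.** No power figure is given for any micro outcome. The stated N = 206 concerns the group-by-time interaction on speech-in-noise perception. The noncentral F calculation (f = 0.10, r = .62, two occasions, alpha 0.05) needs 173 to 174 completers for 85% power. Multiplying by 1.2 gives 208 to 209, within 3% of 206. That figure does not bear on this point.

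**Algebra.** For a given arm, write b for the participant's own level, L(week) for the level carried into the session and A(week) for the within-session response:

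- pre = b + L(week) + e1
- post = b + L(week) + A(week) + e2
- DV_change = post − pre = A(week) + e2 − e1

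L(week) drops out whatever its size. The cancellation is exact for an additive shift shared by both values. Group-by-time on DV_change is a test on A(week) only.

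**Inputs for the numerical check.**

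- From the documents: 210 participants, 1:1 allocation and 20% attrition, so 210 × 0.8 / 2 = 84 per arm; alpha 0.05.
- Borrowed: r = .62 for the correlation of levels across weeks. The protocol uses this value for speech-in-noise, not for HRV or IOS, so 0.5 to 0.8 is also shown.
- Assumed: total SD 1, with variance .62 between persons, .18 between sessions within person and .20 residual (so the within-session correlation is .80); between-arm growth of 0.3 or 0.5 SD from Week 2 to Week 11; no clustering by group or site.

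**Simulation.** 4000 trials per scenario, each contrast tested by a two-sample comparison of Week 11 minus Week 2. Each cell gives the rejection rate for growth of 0.3 / 0.5 SD.

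| What changes in the singing arm | DV_change, group × time | Pre-session level, group × week |
|---|---|---|
| Level shared by pre and post | 4.7% / 5.4% | 61% / 96% |
| Within-session response grows | 57% / 95% | 5.6% / 5.3% |

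In the first row the group main effect on DV_change is no help either: 4.7% / 4.9%. The two models answer different questions, and each is blind to the other's.

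**Power of a level contrast, closed form.** SD of change = sqrt(2 × (1 − r)); noncentrality = growth / (SD of change × sqrt(2/84)). At r = .62 the SD of change is sqrt(0.76) = 0.872.

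| Growth | r = 0.5 | r = .62 | r = 0.8 |
|---|---|---|---|
| 0.3 SD | 49% | 61% | 87% |
| 0.5 SD | 90% | 96% | >99% |

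**The case against.** Much of the case on the other side stands, and it limits the point.

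- **A reader might infer that difference scores cancel every kind of build-up.** They do not. A within-session response that strengthens over the weeks is one legitimate sense of longitudinal impact, and group-by-time detects it (57% / 95% above). Only change in level is lost. If level growth is made up of small session gains that persist, the group effect on DV_change has some power, though little: about 10% / 16% in the same simulation.
- **A reader might infer that the closeness hypothesis cannot be tested as planned.** The cumulative purpose names physiological measures only. Aims and hypotheses frames the micro outcomes as pre- to post-session effects, and H2 mentions no growth over weeks, so DV_change fits its natural reading.
- **A reader might infer that a cumulative social benefit would be missed altogether.** Social connectedness is also measured by the SCS-R at baseline and completion and modelled in levels by group and session. It is a different instrument from the IOS, which asks about the assigned group, but the benefit is not left without any model.
- **A reader might infer that rising closeness will look like a fading effect because of the 7-point ceiling.** The documents give no IOS means. In an illustration, a latent gain of 0.5 was observed as 0.49, 0.47 and 0.37 at mean levels 4, 5 and 6, so the distortion matters only near the top of the scale.
- **HRV synchrony is one value per session and could be followed across weeks.** This is true, although the text says that every micro measure is differenced and gives no model for it.
- **Level models for an exploratory measure may sit in a fuller analysis plan.** Possibly. But this article does state the dependent variable and the model formulas, and those are what fail to match its own purpose.

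**Conclusion.** The point holds for resting HRV. The stated cumulative purpose has no stated analysis that could answer it, because an additive level shift shared by the pre- and post-session values cancels exactly and is flagged at about 5% whatever its size. This follows from the algebra and does not depend on the assumed correlations. The power figures for a level model do depend on them, and on ignoring group and site clustering; they are illustrations, not planning values.

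For IOS the same blind spot exists only if H2 is meant to include closeness that builds over weeks. The documents do not say so, and the stronger claim that a confirmatory hypothesis is unanswerable is not supported. The speech-in-noise analysis is untouched. The consequence is limited to an exploratory measure and the wording of one purpose, but it is cheap to settle before data are seen.

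**What to change.** Keep the DV_change models for the within-session effect. Add, for resting HRV and optionally for IOS, a separate model of the pre-session level: `DV_pre ~ group * week` (Weeks 2, 7 and 11) with a participant random intercept. Label it exploratory for HRV. Alternatively, narrow the second purpose in Micro timepoint testing to change in the within-session response.

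One joint model of pre- and post-session values with only a participant random intercept is not a good substitute. It pools within-session and across-week residual variance. Under the variances assumed above, three of the five within-person degrees of freedom carry .20 and two carry .20 + 2 × .18 = .56. The pooled value is (3 × .20 + 2 × .56) / 5 = .344. The standard error of the group-by-phase contrast (phase meaning pre or post) would then be sqrt(.344 / .20) = 1.31 times the correct one, about 31% too large.

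The report should note that Week 2 is the first micro measurement. Growth before then cannot be separated from a group difference in level.

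The cost is a change of wording and one extra reported contrast per outcome; no new data are needed.

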### Training procedure

Participants will be randomly assigned to either the group singing or audiobook club intervention. Training will occur once-a-week over a total duration of 12-weeks, with each training session lasting approximately 1.5-hours, including informal networking and discussion. Adherence to the intervention will be reported.

Group singing will be facilitated by a choir master with at least one-year of experience leading a choir, a piano accompanist, and support from up to two research assistants who will sing with the participants. The broad goal of the group singing is to provide synchronous vocal pitch training in a supportive and casual environment. The beginning of each session will involve approximately 15-minutes of warm-up exercises, and the repertoire will be decided through discussion between the choir master and participants. Given the choir master will have some flexibility and need to adapt the sessions depending on group ability, a full outline of each lesson will be provided as supplementary materials in the final report. Participants will also be assigned an individual online ‘homework’ task each week—one-hour of using pitch-based games in Theta Music Trainer (https://trainer.thetamusic.com), an application designed for ear training and music theory [118]. The goal of the homework task is to maximize pitch-based perception. Theta Music Trainer provides logging capability that will allow us to monitor participants’ weekly homework tasks. Email reminders will be sent to encourage participant adherence.

Participants in the audiobook club will listen to a 1-hour length audiobook segment prior to each audiobook club session. Participants will be provided with a pool of 10 audiobooks with a brief description on genre and plot. Each audiobook club will collectively select which audiobook/s they would like to listen to during their 12-week intervention. Given they are expected to listen to ~1-hour per week; the audiobook/s must total approximately 12-hours in total duration. The pool has been selected to cover a wide range of genres and interests, and are available in English, German, and Dutch. These sessions will feature a facilitator that will constructively guide the participants through a series of open-ended questions developed by the research team that has been designed to elicit open and constructive discussion. Up to two research assistants will also be present and contribute to the discussions. Email reminders will be sent to encourage participant adherence to the weekly audiobook segment.

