### Macro-level hypotheses

H1. Group singing may be associated with better music perception such as pitch, rhythm, timbre, and higher-level music skills—more so than participants in the control group.H2. Group singing may be associated with better speech perception such as speech-in-noise and emotional prosody—more so than participants in the control group.
The mechanism for speech perception enhancement may be due to improvements in music perception (i.e., pitch, rhythm, timbre, or higher-level music skills.)H3. Group singing may be associated with better psychosocial health—more so than participants in the control group.
The primary outcome of interest is the enhancement of quality of life and social connectedness.The secondary outcomes of interest are the reduced symptoms of depression and anxiety, and the enhancement of self-esteem.

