#### Music perception materials

A Frequency Difference Limen (FDL) task will be used to evaluate pitch perception. Participants will be presented with a three-alternative forced choice (3AFC) paradigm containing two pure tones (200 ms in duration, with 20 ms envelope rise and fall times) at 500 Hz, with the target stimulus adaptively presented at a higher frequency. The participant will identify which corresponding tone is higher on a computer keyboard (i.e., the first, second, or third tone). A pitch discrimination threshold will be calculated with an adaptive staircase procedure with the frequency difference between the target and 500 Hz tones divided by two after three correct responses, or multiplied by two after one incorrect response. After five reversals, the step size will change, with the frequency difference divided by 1.414 after 3 correct responses or multiplied by 1.414 after one incorrect response. Participants will complete two-blocks, with each block ending after 12 reversals. The calculation of their FDL threshold is determined from the mean of the last 10 reversals of each block, which were then averaged between the two blocks.

The Beat Alignment Test (BAT) will be used to measure musical beat perception and rhythm [107]. The BAT consists of 36 musical excerpts that are played with a superimposed click track in three conditions that are: 1) “On beat”—on the beat; 2) “Off beat”—off the beat with the wrong tempo; and 3) “Phase error”—out of phase. Participants will be provided with practice trials. The task is to identify if the excerpt is on the beat by responding on a keyboard with YES or NO. Participants will be instructed not to tap or move along to the music.

The Spectral-temporally Modulated Ripple Test (SMRT) is a measure of spectral resolution [108], which will be used as a proxy measure of timbre perception. Compared to typical spectral resolution tasks, the SMRT features dynamically changing ripples. Participants will be presented with a three-alternative forced choice (3-AFC) task. The target choice is presented at an initial presentation of 0.5 ripples per octave (rpo), while the other two choices are presented at a reference stimuli of 20 ripples rpo. The target stimuli are modified with a 1-up 1-down adaptive procedure with a step size of 0.2 rpo. After 10 reversals, a threshold is derived from the average of the last six reversals.

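### The experimental arm is group singing plus solo pitch homework, so a difference in pitch threshold or speech-in-noise cannot be credited to singing alone

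*Protocol article*

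**What the plan says.** All references are to the Protocol article.

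- **Sessions (Training procedure).** "Training will occur once-a-week over a total duration of 12-weeks, with each training session lasting approximately 1.5-hours". That time includes informal networking and discussion.
- **Homework, singing arm (Training procedure).** Each participant is assigned, every week and individually, "one-hour of using pitch-based games in Theta Music Trainer". The purpose is explicit: "The goal of the homework task is to maximize pitch-based perception". The app logs use so that homework can be monitored, and adherence is to be reported.
- **Homework, control arm (Training procedure).** "Participants in the audiobook club will listen to a 1-hour length audiobook segment prior to each audiobook club session". Over the programme this comes to about 12 hours.
- **Pitch outcome (Music perception materials).** "A Frequency Difference Limen (FDL) task will be used to evaluate pitch perception". It is an adaptive three-alternative threshold for pure tones around 500 Hz.
- **H1 (Macro-level hypotheses).** "Group singing may be associated with better music perception such as pitch, rhythm, timbre, and higher-level music skills", more so than in the control group.
- **H2 (Macro-level hypotheses).** "Group singing may be associated with better speech perception such as speech-in-noise and emotional prosody", again relative to control, with a proposed route: "The mechanism for speech perception enhancement may be due to improvements in music perception".
- **Rationale for the control (Study design).** The audiobook club is justified as a comparator suited to studying the specific benefits of singing in synchrony as a group.
- **Analysis (Modelling and inferential statistics; Mechanisms and contributions to speech perception).** The macro models contain group and session only. If speech perception improves, change in FDL, the Beat Alignment Test (BAT) and the ripple test (SMRT) is used to explain that improvement.

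**The concern.** The hypotheses name one cause, group singing, but the arm that tests them contains two: group singing, and solo computerised pitch training that is neither sung, nor done in a group, nor synchronised. The second component is aimed at pitch perception. Pitch is the first skill listed in H1, and it is one of the routes by which H2 expects speech-in-noise to improve. The Introduction gives that route weight, citing an earlier choir study in which the speech-in-noise gain was mediated by better pitch discrimination.

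A participant who gains little from the choir but improves through the games would still contribute to a group-by-session interaction on FDL, and the plan's wording would record that as a benefit of singing. The same applies to a speech-in-noise gain that runs through FDL. At stake is the attribution in the trial's conclusions on pitch and speech. The validity of the randomised comparison is not in question.

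**Working it through.** **1. Assigned exposure in the singing arm**

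- Sessions: 12 × 1.5 h = 18 h (networking and discussion included; their share is not stated).
- Pitch games: 12 × 1 h = 12 h.
- Share: 12 / (18 + 12) = 12/30 = 40%.
- Control arm: also 18 h of sessions and about 12 h of homework, with no assigned pitch training.

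The arms are matched on homework time and differ in its content.

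**2. What the two-arm contrast can identify**

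| Arm | Group activity | Homework |
|---|---|---|
| Singing | choir | pitch games |
| Control | audiobook discussion | audiobook listening |

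Activity and homework change together. No arm has singing without the games or the games without singing, so the group term carries the sum of both. A larger sample does not help. Adjusting for logged app hours does not restore a randomised comparison either, because use is determined after randomisation and exists in one arm only.

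**3. The plan's own sample size, as a basis for an illustration**

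Inputs from Statistical power analysis: f = 0.10, α = 0.05, r = 0.62, two time points, 85% power, 20% attrition, N = 206. For the within-between interaction, λ = f² × N × 2 / (1 − r), with 1 and N − 2 degrees of freedom.

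- N = 172 gives power 0.849; N = 174 gives 0.853.
- 172 × 1.2 = 206.4, so the stated 206 is reproduced when attrition is added as 20% of the completers. Dividing by 0.8 would give 215 (172/0.8) to 218 (174/0.8).
- The planned 210 less 20% leaves 168 completers: λ = 0.01 × 168 × 2 / 0.38 = 8.84, power 0.84.

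**4. Illustration: singing has no effect on speech-in-noise and the homework has some**

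The documents give no figure for the homework's effect, so f for homework is an assumption, shown over a range. With 168 completers and r = 0.62:

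| Homework-only f (assumed) | λ | Probability of a significant group × session test |
|---|---|---|
| 0 | 0 | 0.05 |
| 0.02 | 0.35 | 0.09 |
| 0.04 | 1.41 | 0.22 |
| 0.06 | 3.18 | 0.43 |
| 0.10 (the planned effect) | 8.84 | 0.84 |

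In every row below the first, a significant result would be produced partly or wholly by the homework, and H2 as worded would read it as singing. The table shows what the design cannot distinguish; it does not predict what will happen. It uses the planning values for speech-in-noise; the article gives none for FDL.

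**The case against.** The strongest reply is that the intervention is the package. The article discloses the homework, its weekly dose and its aim, and the randomised contrast validly estimates the effect of that arm against the control arm. This stands. A reader might infer that H1 and H2 cannot be answered at all; the documents do not support that, since both can be answered for the package. What remains is that the hypotheses and the control rationale describe the package as group singing.

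Several other limits also stand:

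- A reader might infer that the games rehearse the FDL task itself. The article does not describe the games beyond their being pitch-based and part of an ear-training and music-theory app. The overlap shown is of construct (pitch perception), not of task format. The choir sessions are themselves meant to train pitch, so both components act on it.
- The 12 hours are assigned, and actual use may be lower.
- The control arm does have homework, matched in time. This is not an imbalance in contact or effort.
- The point is strongest for FDL and the pitch route to speech-in-noise. It is weaker for BAT, SMRT, the Music-in-Noise Task and the vocal emotion test, although the components are inseparable there too.
- A reader might extend it to H3 or the micro-level hypotheses. Nothing in the article suggests that solo pitch games drive quality of life or social connectedness, and the micro-level outcomes are changes within a single session.
- Whether better pitch perception accompanies better speech-in-noise can be studied whichever component improved pitch. Only the further step, crediting singing, is affected.

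Planned adherence reporting and app logs do not answer the remaining point, because a description of use cannot separate two components that every participant in one arm is assigned.

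**Conclusion.** The concern holds for attribution. By design the experimental condition is group singing plus about 12 assigned hours of solo pitch games, 40% of that arm's 30 assigned hours, against time-matched listening in the control arm. An arm difference on FDL, and any speech-in-noise difference (above all one explained through FDL change), cannot be credited to group singing apart from the homework. H1, H2 and the control rationale word it as if it could.

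This rests on the article's description of the two arms and on the absence of any arm or model term that separates the components. It does not depend on how effective the games are. How large the misattribution could be does depend on that, and the documents are silent: under the assumed range above, the chance that the homework alone yields a significant speech-in-noise interaction runs from 0.09 to 0.84.

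**What to change.** Leave the intervention, sample size and models as they are, and change what is claimed.

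1. In the objective, H1, H2 and the conclusions, define the experimental arm as *group singing plus weekly computerised pitch training*, and bring the control rationale into line.
2. State that the homework targets the same construct as FDL, so that an arm difference on FDL, and a speech-in-noise result mediated by FDL, is not specific to singing.
3. Optionally, report FDL and speech-in-noise change against logged app hours and session attendance, labelled as a non-randomised description.
4. For H3 and the micro-level hypotheses, use the same description of the arm; their claims need no rewriting.

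The cost is a few sentences and, if item 3 is adopted, one descriptive analysis of app logs and attendance. The real price is a narrower headline: the trial would speak to the combined programme and not to group singing alone.
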